*Decision support* will be addressed through multiple decision support tools. A triage instrument is used for stratification (as mentioned above), as well as to provide a suitable level of care and support intensity as offered by the ECT. The second decision-support instrument is a structured history questionnaire based on the results of a Delphi study with a panel of 41 experts (as yet unpublished). This study resulted in a set of 30 categories selected from the International Classification of Functioning, Disability and Health (ICF) [42], regarded as the most common health-related problems of community-living people aged 75 years and older (without dementia). Each topic needs to be assessed by the individual elderly person in the *frail* and *complex care needs profiles.* Assistance in filling out this form will be provided by the case manager during the first home visit. Links to the ICF Browser (for additional categories in the history questionnaire) and to the official guidelines of the Dutch College of GPs (to support evidence-based guidelines) are embedded in the clinical information system.

The *clinical information systems* will be represented by the Electronic Elderly Record System (EERS), a web-based application built for both clinical and research purposes. This computer program is based on work by colleagues who developed a systematic approach to identify patients with complex care needs by scoring the patient and to subsequently systematically document the information [43]. In clinical practice, the EERS will facilitate the ECT members in providing effective care and support. Therefore, the EERS will include personal health records that contain individual triage data, the history questionnaire, an individual care and support plan with information about goal setting, actions performed, and evaluations. For team management purposes, the EERS contains a panel overview and a team agenda. For research purposes, the EERS will be used to evaluate Goal Attainment Scaling (GAS) in the care and support plans, as well as the time expenditures of the ECT members.

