*Perceived chronic illness care* will be evaluated using the Patient Assessment of Chronic Illness Care (PACIC) [51]. It reflects on all CCM elements and evaluates – from the elderly participants’ perspective – the degree to which integrated care is realized. Originally, the PACIC was developed for people with a specific chronic disease. Since the PACIC will be applied to a population of elderly persons, the disease-related items in the Dutch version of the PACIC [52] will be rephrased into questions more suitable for an ageing population.

*Self-management knowledge and behavior* will be measured with the Partners in Health scale (PIH) [53]. It assesses self-management knowledge and behavior regarding one’s chronic condition. For this study, the English PIH version will be translated into Dutch using forward and backward translation [54] and modified for the elderly population by rephrasing items.

The primary outcome regarding the *cost analysis* is the cost utility expressed in Quality Adjusted Life Years (QALYs) that will be calculated using the health status (EQ-5D) [48] and service use of participants.

*Service use* will be assessed using the Minimal Data Set-economic evaluation (MDS-e) patient self-report questionnaires. This is a set of questions evaluating a wide spectrum of services used during the previous twelve months. The questions focus on hospital stay and ER admissions, nursing-home stay, GP visits, home health care, assist devices acquired, and home adjustments. Standardized cost prices will be used to calculate the costs of services used. If possible, data will be used from databases of health insurers and municipalities.

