### Statistical analysis

Descriptive statistics will be used to assess differences between intervention and control groups concerning basic characteristics and confounding variables.

Analyses of the effects regarding primary and secondary outcomes will be executed using the “intention-to-treat principle” [60]. The first analyses will focus on the differences between intervention and control groups after intervention, on the level of the sample and on the level of the strata, with respect to the primary and secondary outcomes. T-tests or (M)ANOVA will be used for continuous variables, Chi square tests, the Wilcoxon tests, and difference of proportions tests for discrete variables. Analysis for change in caregiver burden will focus on the differences between baseline and follow-up measurements by means of Wilcoxon tests, taking into account the duration of support in months. Clinical relevance of the effects will be estimated by Cohen’s effect sizes for statistically significant group differences (p < 0.05).

The incremental cost-effectiveness ratio will be calculated as total costs per QALY [61], and total costs per patient outcome measurement. Bootstrapping will be used to determine the confidence interval. Discounting will initially not be applied considering the limited follow-up period.

For calculation of the GAS, the method proposed by Rockwood [62] will be applied. The first step in this method is to relate the separate problem target scores to the achieved end scores. Next, three specific analyses are performed: 1) calculation of each individual problem score, 2) calculation of overall problem score for each patient, and 3) calculation of the sample score. Finally, the standardized GAS score is used to measure the extent to which the goals were achieved.

The psychometric properties of the PACIC [51] and PIH [53] will be analyzed separately, since these measurements were translated and modified for the current study. For the psychometric evaluation, we will employ confirmatory factor analysis and will estimate the reliability by calculating internal consistency. Criterion validity will be estimated with known-groups comparisons.

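### The cost-effectiveness ratio is called incremental, but its stated formula contains no between-arm difference, and the plan does not say whether Embrace's own delivery costs enter the cost side

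*Protocol article*

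**What the plan says.** In the protocol article, *Statistical analysis*, the rule for the economic comparison is: "The incremental cost-effectiveness ratio will be calculated as total costs per QALY [61], and total costs per patient outcome measurement". The next sentence is "Bootstrapping will be used to determine the confidence interval".

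*Primary outcome measurements* makes cost utility the primary outcome of the cost analysis, in QALYs "that will be calculated using the health status (EQ-5D) [48] and service use of participants". Service use comes from the MDS-e self-report questionnaire: "The questions focus on hospital stay and ER admissions, nursing-home stay, GP visits, home health care, assist devices acquired, and home adjustments". The costing rule is "Standardized cost prices will be used to calculate the costs of services used", followed by "If possible, data will be used from databases of health insurers and municipalities". *Secondary outcome measurements* plans cost-effectiveness against complexity of care needs, frailty and functional status, using the same cost sources.

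*Intervention: Embrace* says the electronic record system (EERS) will be used in research to evaluate goal attainment, "as well as the time expenditures of the ECT members". *Data collection* lists the EERS as a data source. No section says that this time is priced and added to costs, and none says that it is excluded.

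**The concern.** Three things are left open for a declared primary outcome.

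1. **The ratio.** An incremental ratio divides a difference in mean cost by a difference in mean effect. The written formula has neither difference. Followed to the letter, it gives an average ratio, which answers another question. The second half of the sentence is harder to rescue. On IM-E-SA, GFI and the modified Katz index a higher score is worse, so cost per point has no sensible direction.
2. **The costs.** Case-manager contacts, monthly team meetings, training, community meetings and the record system are Embrace activities. None appears among the cost inputs. Leaving them out would bias the comparison in favour of Embrace.
3. **The uncertainty.** If the bootstrap interval is taken on the ratio, it loses its meaning once an appreciable share of replicates has a QALY difference at or below zero. The Discussion itself concedes that one year might be insufficient to show effects, cost-effectiveness included.

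**Working it through.** The documents give no cost, QALY or ratio value, so there is no plan figure for the ratio to reproduce. All economic inputs below are assumptions, in euros. Group sizes come from *Sample size*: 2178 × 0.70 × 0.70 = 1067 retained, or about 533 per arm. Stratum B at 16% gives 171, or about 85 per arm, which agrees with the stated 85 if that is read per arm.

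**Average against incremental ratio.** Assume mean cost and QALY of 21,500 and 0.72 under Embrace, and 20,000 and 0.70 under usual care.

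- Average ratios: 21,500/0.72 = 29,861 and 20,000/0.70 = 28,571.
- Incremental ratio: (21,500 − 20,000)/(0.72 − 0.70) = 1,500/0.02 = 75,000 per QALY.

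With 11,000 and 0.72 against 10,000 and 0.70, the average ratios are 15,278 and 14,286, and the incremental ratio is 1,000/0.02 = 50,000.

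**Direction of the outcome scales.** For a score S on which higher is worse, total cost per point is C/S. At fixed cost C, this rises as S falls, so improvement looks more expensive per point.

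**Delivery costs.** Table 1 gives about 1 structured contact a month (frail) or 2 (complex care needs) for 6–12 months, so 6–12 or 12–24 contacts. Assume 50–100 per contact. Omitting a cost k per Embrace participant lowers the ratio by k/ΔQ, where ΔQ is the QALY difference.

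| Profile | k per person | Shift at ΔQ = 0.02 | Shift at ΔQ = 0.05 |
|---|---|---|---|
| Frail | 300–1,200 | 15,000–60,000 | 6,000–24,000 |
| Complex | 600–2,400 | 30,000–120,000 | 12,000–48,000 |

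Team meetings, training and the record system would add to k.

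**Interval on the ratio.** Assume a cost difference of 1,000, SD of cost 15,000, SD of QALY 0.2, and independent normal draws of the two differences (200,000 draws).

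| Per arm | ΔQ | Share with difference ≤ 0 | 2.5th to 97.5th percentile of ratio |
|---|---|---|---|
| 85 | 0.01 | 37% | −961,000 to 1,012,000 |
| 85 | 0.02 | 26% | −837,000 to 864,000 |
| 85 | 0.05 | 5% | −228,000 to 322,000 |
| 530 | 0.01 | 21% | −1,031,000 to 1,124,000 |
| 530 | 0.02 | 5% | −272,000 to 485,000 |
| 530 | 0.05 | below 0.01% | −17,000 to 69,000 |

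The last row is usable. The others are not, because a negative ratio can mean cheaper and better or dearer and worse.

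**Second set of assumptions, and the effect of baseline adjustment.** Take utility SD 0.25, T0–T1 correlation 0.6, QALY as the mean of the two utilities, and a true gain of 0.025.

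- Unadjusted: SD = 0.25 × √((1 + 0.6)/2) = 0.224. SE = 0.224 × √(2/85) = 0.0343, and 0.0137 at 533 per arm. The chance of a difference ≤ 0 is 23% in stratum B and 3% overall.
- Adjusted for T0 EQ-5D: SD = 0.25 × √(1 − 0.36)/2 = 0.10. SE = 0.10 × √(2/85) = 0.0153, and 0.0061 at 533 per arm. The chance falls to Φ(−0.025/0.0153) = 5% in stratum B and below 0.01% overall.

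**The case against.** The strongest reply is that this is condensed wording, not a wrong plan. The measure is named incremental, the outcome analyses are framed as comparisons between arms, and the Discussion speaks of costs in one group against the other. The formula may simply be naming units, with a methods reference behind it. Bootstrapping is standard in economic evaluation, and planes or net-benefit displays are often left to an analysis plan. Team time is logged for research and is not an outcome in Table 2, so costing is a plausible purpose. Some nurse visits could be reported as home health care, or be captured in insurer data.

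Much of this stands, and it rules out three stronger inferences.

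- **That ratios will be computed within each arm.** The label and context point the other way. What remains is that the written rule and its label disagree.
- **That delivery costs are omitted.** No section excludes them, and the MDS-e list describes a patient questionnaire, not a closed definition of total cost. What remains is that the route from logged time to cost is not stated, and that training, community meetings and the record system are not mentioned as costs.
- **That the bootstrap is invalid or the economic conclusion wrong.** The type of interval is not stated, stratum-level ratios are not explicitly planned, and the ratio interval works when the QALY difference is clearly away from zero.

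The reply does not remove the point, because the article does state a formula and does list cost inputs, and both can be followed in ways that give different answers.

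**Conclusion.** The point holds as a defect in what is written. The stated formula for a primary outcome does not match its label, it has no usable direction for the three outcome scales on which higher is worse, and the cost inputs do not say that Embrace's own delivery is counted. The bias in favour of Embrace is conditional on those costs being left out. The interval problem is conditional on a small QALY difference, which the protocol's own remarks on short follow-up make plausible, especially by stratum.

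The size cannot be fixed from the documents. Under the assumptions shown, the gap between average and incremental ratio is tens of thousands of euros per QALY. Omitted contacts alone could shift the ratio by 6,000 to 120,000 per QALY. The share of replicates with no QALY gain runs from almost none to more than a third.

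**What to change.** Amend the economic paragraph before the analysis begins; *Trial status* says that is imminent.

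- **Ratio.** Define it as (mean cost Embrace − mean cost usual care)/(mean QALY Embrace − mean QALY usual care). For the other outcomes use the difference in mean score, with the direction of benefit stated so that a positive denominator means improvement.
- **Baseline.** Adjust incremental QALYs for T0 EQ-5D. It is already collected, is not among the balancing criteria under *Randomization*, and enters a two-point QALY directly.
- **Costs.** State that EERS-logged team and case-manager time is priced and added to intervention-arm costs, together with training, community meetings and the record system. Say how double counting with self-reported home care or insurer data is avoided.
- **Uncertainty.** Bootstrap the incremental net monetary benefit, λΔQ − ΔC, over a stated range of willingness-to-pay values λ. It is defined for any ΔQ. Report its 95% interval and show the replicates on the cost-effectiveness plane.

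The cost is some extra analysis work, mostly with data already recorded; unit prices and the training and system costs must be gathered. The result may be less favourable to Embrace.

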### Trial status

The first intervention year has ended and follow-up measurements were completed. Data analyses will start soon.

## Discussion

To our knowledge, the Embrace study is the first RCT that studies the effectiveness, including cost-effectiveness, of an integrated care model that is based on all CCM elements and is applied to a community sample of elderly people.

Previous studies have shown that implementing specific elements of the CCM positively influences outcome variables, but few studies have investigated the effect of applying all elements simultaneously, and most studies concerning the CCM have lacked a solid study design. Furthermore, the CCM has been tested in specific disease populations, but we found no studies in which the effectiveness for the elderly population in general was investigated. In this respect, our Embrace study is unique.

To establish unambiguously the effectiveness of Embrace, a design was developed with a large contrast between intervention and care as usual, with a focus on stratification and blinded randomization of participants, selection of valid and reliable measurement instruments that are sensitive for change, control for confounders, and an adequate sample size. We argue that the current design contains all these.

A few limitations should be mentioned as well. First, the follow-up period may be too short to demonstrate (cost-) effectiveness. Embrace represents a major structural adjustment to an existing system of care, and so requires cultural adaptation. Therefore, it may take time for significant effects in service use and costs to become measurable. This so-called “investment effect” implies that in the first year of an intervention, the health care costs in the experimental group usually are higher than in the usual care group, while intervention benefits will become visible in subsequent years [41,63]. In addition, chronic conditions tend to fluctuate in severity [64]. Multiple measurement moments spread over several years would be preferable. Consequentially, we will attempt to prolong the follow-up period in order to measure the true long-term effectiveness of Embrace.

Another limitation is the risk of selection bias. Elderly people with a poor health status may be less likely to decide to participate [65]. This effect could be reinforced by the length of the questionnaire [66], as well as by the relatively low socioeconomic status and limited (health) literacy in the participating municipalities [67]. Interventions to counteract this risk of selection bias have been built into the data-collection procedure.

Finally, although the design is as strong as possible, we have to deal with potential design bias. Participants will be balanced within GP practices, mainly due to implementation reasons: all participating GPs will be trained in working according to Embrace. Therefore, it is conceivable that participants in the control group will also receive more proactive and preventive care and counseling. However, this risk for contamination is considered to be trivial because the intervention contrasts so strongly with the usual care provided by a GP: a regular GP visit tends to be rather brief and normally takes about 10 minutes [68], with only a small amount of time available for assessment of (potential) health problems or topics [69].

In conclusion, we have started a RCT that will assess the effects of Embrace regarding patient outcomes, service use, costs, and quality of care in a population of community-living elderly. We hope to demonstrate that patient centered, comprehensive, proactive, and preventive care and support, as structured by Embrace, will be a solution to the challenges current health care systems are facing.

## Abbreviations

ACIC: Assessment of Chronic Illness Care; (I)ADL: (Instrumental) activities of daily living; CCM: Chronic Care Model; CSI: Caregiver Strain Index; ECT: Elderly Care Team; EERS: Electronic Elderly Record System; EQ-5D: EuroQOL, health related quality of life, five dimensions; GAS: Goal Attainment Scaling; GFI: Groningen Frailty Indicator; GP(s): General practitioner(s); GWI: Groningen Well-being Indicator; ICF: International classification on functioning, disability and health; IM-E-SA: INTERMED Elderly Self-Assessment; KP-triangle: Kaiser Permanente triangle; MDS-E: Minimal data set economic evaluation; NZa: Dutch healthcare authority; PACIC: Patient Assessment of Chronic Illness Care; PHR: Personal health records; PIH: Partners in Health Scale; QALY: Quality Adjusted Life Years; RCT: Randomized controlled trial; SMAS-30: Self-Management Ability Scale-30; VAS: Visual Analogue Scale; ZonMw: Dutch organization for health research and development.
